***Qualitative Analysis***

Transcripts will be reviewed for emerging themes using an iterative process of textual analysis. The constant comparative method will be used to identify and refine codes and devise a final code structure.^134^ Transcripts will initially be read in their entirety to gain insight into broad themes and to note repeating themes. Themes and subthemes will be reviewed to confirm consistency, coherence, and distinctiveness before defining and finalizing a codebook that reflects the data’s meaning. Each reader will do multiple passes to get the full picture of discussion flow and consensus will be reached for each quotation. Data organization and retrieval will be facilitated by Dedoose software.

***Data Synthesis***

Through triangulation, a process for strategically utilizing both methods together, we will examine convergence and expansion.^135^ Convergence assesses whether quantitative and qualitative results provide the same answer to the same question (e.g., does quantitative assessment of barriers concur with qualitative data around barriers/facilitators of implementation). Expansion assesses whether the qualitative data can explain unanticipated findings produced by quantitative data (e.g., can quantitative data that suggests little variation in clinic structures across different types of clinics be further explained by qualitative data).

## Statistical Hypotheses

***Effectiveness***

*Null Hypothesis (H0):* The integrated HS+PlayReadVIP intervention does not significantly improve parenting practices and relational health outcomes compared to HS alone.

*Alternative Hypothesis (H1)*: The integrated HS+PlayReadVIP intervention significantly improves parenting practices and relational health outcomes compared to HS alone.

***Implementation***

*Null Hypothesis (H0)*: The HS+PlayReadVIP intervention is not feasible, acceptable, appropriate, or scalable in real-world pediatric primary care settings.

*Alternative Hypothesis (H1)*: The HS+PlayReadVIP intervention is feasible, acceptable, appropriate, and scalable in real-world pediatric primary care settings.

## Analysis Datasets

The project will produce data obtained from surveys/questionnaires, interviews, direct assessments, and observations. Data will be collected from ~500 parent-child dyads, generating several raw datasets. Data will be collected and stored in secure REDCap databases. Datasets will be merged for analysis and stored in CSV format. We will produce raw data files to be transformed into final datasets for statistical analysis at the individual level.

## Description of Statistical Methods

For general and primary endpoint analytic methods, see above.

### Safety Analyses

Summary statistics for AEs and SAEs will be examined. AEs will be coded according the severity (see Section 8.2.1), and the number, severity, frequency, and relation to the study will be presented to the DSMB and other audiences of interest.

### Adherence and Retention Analyses

Participant engagemet in the intervention (e.g., number of possible sessions attended) and fidelity of intervention delivery (e.g., number of program components delivered at each session) will be tracked from the medical record and presented using summary statistics. As noted above, missing data and attrition analyses will be conducted to determine if data is missing at random or missing completely at random, and multiple imputation will be used to account for missing data.

### Baseline Descriptive Statistics

Intervention and control groups will be compared at baseline for differences in sociodemographic characteristics, including child gender, parity, maternal education, income, and mental health, using omnibus F-tests, t-tests, and chi-square tests.

### Planned Interim Analysis

#### Efficacy Review

The same analyses described above will be conducted after assessments at 12 months to examine efficacy outcomes after 6-12 months of intervention delivery. This analysis will not impact final efficacy analyses, although we will address the potential higher rate of type I error due to multiple comparisons (multiple parent and child characteristics), we will use the false discovery rate approach.

### Multiple Comparison/Multiplicity

As noted above, we will use the false discovery rate approach to correct for the potential higher rate of Type I error due to multiple comparisons.

### Tabulation of Individual Response Data

Individual participant data will be listed by measure and time point, and datasets will be available in both wide and long form.

## Sample Size

Sample size was estimated based on a cumulative attrition rate of 15-20% by 24M, similar to previous studies of PlayReadVIP in New York City, and a conservative effect size of HS+PlayReadVIP for main impact analyses of *d* = .30. This effect size is below previous studies of PlayReadVIP alone (*d* = .3-.5), accounting for the potential for non-additive impacts of HS+PlayReadVIP following integration with standard HS. With enrollment of 500 families, we expect a final sample size of 400, which provides more than 80% power to detect an effect size of *d* = ~.3 given alpha = .05 in ANOVA analyses,^166^ a small-to-medium effect size of *f^2^*=.04 in our most complex OLS regression analyses including moderation, and β*_YX_* = 0.3, with only moderate item reliability^167^ in SEM analyses. Our final sample of 400 will provide 80% power to detect a small-to-medium effect size (.26) in mediation analyses based on previous simulation studies.^168^ Analysis of fidelity of delivery will be based on number of sessions (~1125-1500, or 7-10 sessions per family over 2 years), rather than number of families. We have 80% power to detect a small effect size of β*_YX_* = 0.1 in these SEM models.^167^

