### Administration of Intervention

The combined HS+PlayReadVIP model is delivered in person or online with 9 structured sessions from infant age 4 months to 36 months, coinciding with pediatric well-child visits. The program is delivered by trained HS Specialists, with a Masters’ degree or higher. Training ensures fidelity, and sessions are tailored to family needs with flexible scheduling. This approach integrates behavioral and social strategies into pediatric care, minimizing disruption to families and providers.

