***Implementation Outcomes***

Initial analyses will include examination of measure distribution, tests of normality, and confirmatory factor analysis, to create multi-indicator, multi-informant constructs where appropriate. Reach: Effect sizes of differences between 1) the study sample and clinic population, and 2) those who were eligible and enrolled vs. those who were eligible and declined will be determined by descriptive comparisons of multiple sociodemographic characteristics, including race/ethnicity, maternal age, child gender, and income. Fidelity: Summary scores will be created for fidelity data across sessions (i.e., computing proportion of HS and/or VIP session components completed on average, and the interquartile range). Scores will be computed separately for VIP (PCEs related) and HS (ACEs related) content for component analysis to understand whether differential implementation outcomes/challenges occur when HS+VIP is implemented jointly. Engagement: Chi-square tests for independence will be used to examine differences between the proportion of visits attended in the HS+VIP and standard HS models.

Acceptability: To investigate acceptability among parent participants, SEM will be used to examine AIM scores across assessment timepoints and to examine whether trajectories in parent AIM scores vary by participation or sociodemographic characteristics. In addition, multivariate ANOVA will be used to examine acceptability across interested parties at different levels (parents, HS+VIP care team). Finally, confirmatory factor analysis will be used to create a multi-informant acceptability construct and multivariate ANOVA will again be used to examine differences in overall acceptability across HS+VIP and standard HS groups.

Appropriateness: Analysis of appropriateness will mirror analyses used to examine acceptability.

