***Moderation of Implementation Outcomes***

To examine how CFIR individual and intervention-related factors predict implementation fidelity, multivariate regression analysis will be used. We will regress fidelity outcomes (fidelity in delivery, receipt, and enactment) on parents’ perception about the intervention, family characteristics, and child characteristics. Three fidelity outcomes will be examined in separate analyses.

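### The 80% power claimed for the fidelity analysis counts sessions with no allowance for correlation within families, and the session count does not match the enrolled arm

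*Protocol*

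**What the plan says.** Protocol Section 9.5 (Sample Size) states that the fidelity analysis "will be based on number of sessions (~1125-1500, or 7-10 sessions per family over 2 years), rather than number of families". On that basis it claims "80% power to detect a small effect size of" 0.1 in structural equation models. It mentions no intraclass correlation, design effect or multilevel term.

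Three other places bear on the claim:

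- Section 9.1, Implementation Outcomes, defines the fidelity variable: "Summary scores will be created for fidelity data across sessions".
- Section 9.1, Moderation of Implementation Outcomes, plans multivariate regression of fidelity on parents' "perception about the intervention, family characteristics, and child characteristics".
- Section 6.1.1 (Administration of Intervention) describes "9 structured sessions from infant age 4 months to 36 months". Sections 6.1 and 7.1.1 have delivery run to 24 months.

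The trial randomises 500 families to two arms and expects 400 at the end (Sections 4.1 and 9.5).

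**The concern.** Sessions from one family share a parent, a child and probably a provider, so their fidelity scores are likely to be correlated. When a predictor takes the same value for all or nearly all sessions of a family, the information about it is governed mainly by the number of families. Adding sessions helps only so far as they are not correlated. If the outcome is a single summary per family, extra sessions add no units at all.

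Section 9.5 counts sessions and explicitly sets the number of families aside. The effect the analysis can detect may therefore be about twice the stated one, and a null result for a predictor of fidelity could be given more weight than it can bear. The session count itself also does not follow from the enrolled arm size and the stated sessions per family.

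**Working it through.** **Inputs.** Section 9.5 gives 1125-1500 sessions, 7-10 per family, a coefficient of 0.1, power of 80%, 500 families enrolled and 400 at the end. Alpha of .05 is stated there only for another calculation ("given alpha = .05 in ANOVA analyses"); I assume it here, two-sided. Section 9.6.1 limits the imbalance between arms to 4, so I infer about 250 enrolled and 200 retained per arm. The documents give no ICC, so every ICC below is an assumption.

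**1. The stated figure.** For a standardised coefficient r, the number of independent units needed is n = ((1.960 + 0.842)/atanh(r))² + 3. With r = 0.1 this is 783. If sessions were independent and measured without error, power would be 92% at 1125 and 97% at 1500. The stated 80% is therefore met with room to spare, but not reproduced. Assuming a reliability of about .84 (1125 sessions) or .72 (1500) on both variables does reproduce it. That uses up the surplus and leaves nothing for clustering.

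**2. One fidelity score per family.** Here 0.1 is the standardised coefficient for the family score. Power is from the noncentral F for one predictor. The smallest detectable coefficient at 80% is tanh(2.802/√(F − 3)) for F families.

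| Families | Power at 0.1 | Smallest coefficient at 80% power |
|---|---|---|
| 150 | 23% | .23 |
| 200 | 29% | .20 |
| 250 | 35% | .18 |
| 400 | 52% | .14 |
| 500 | 61% | .125 |

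**3. Sessions nested in families.** Here 0.1 is on the session scale. With M sessions, m per family and a family-level predictor, the effective number is M/(1 + (m − 1)ICC). Setting this equal to 783 gives the largest ICC that keeps 80% power: (M/783 − 1)/(m − 1).

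| Families | m | M | Largest ICC |
|---|---|---|---|
| 150 | 7.5 | 1125 | .07 |
| 150 | 10 | 1500 | .10 |
| 200 | 7 | 1400 | .13 |
| 200 | 10 | 2000 | .17 |
| 250 | 7 | 1750 | .21 |
| 250 | 10 | 2500 | .24 |

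For example, 200 families with 7 sessions give (1400/783 − 1)/6 = .13. At an assumed ICC of .3, power at 0.1 is .61 (m = 7) to .645 (m = 10) for 200 families, and .71 to .74 for 250.

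**4. The session count.**

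- Ends matched: 1125/7 = 161 and 1500/10 = 150 families.
- Ends crossed: 1125/10 = 113 and 1500/7 = 214 families.
- Enrolled arm: 250 × 7 = 1750 to 250 × 10 = 2500 sessions.
- Retained arm: 200 × 7 = 1400 to 200 × 10 = 2000 sessions, which overlaps the stated range only at 1400-1500.
- Read the other way, 1125/250 = 4.5 and 1500/250 = 6 sessions per enrolled family, below the stated 7-10.

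**5. The schedules.** Nine sessions lie inside 7-10, but the horizons differ: 36 months in Section 6.1.1, against 24 months in Sections 6.1 and 7.1.1 and two years in Section 9.5. The upper figure of 10 within two years also exceeds the 9 that Section 6.1.1 plans over the longer period.

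**The case against.** The strongest reply is that 783 units suffice, so 1125-1500 sessions already absorb a design effect of 1125/783 = 1.44 to 1500/783 = 1.92. If the count is corrected upward to 250 families, 80% survives up to an ICC of .21-.24. If both arms contribute, which the wording of the fidelity paragraph in Section 9.1 allows, 400 retained families would tolerate about .43-.46. The power claim also rests on a cited tutorial for structural equation models, which need not agree with a simple correlation formula. This much stands: a reader might infer that 80% power is out of reach, and the documents do not support that. It depends on an ICC they do not give and on whether fidelity is scored per session or per family.

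Three further readings should be held back.

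- One might infer that the session count fits no arm size. It does fit about 200 retained families at 7 to 7.5 sessions each.
- One might infer false-positive findings. At an assumed ICC of .3, ignoring clustering would raise a nominal 5% test of a family-level predictor to about 24-31%. But the protocol nowhere says that sessions will be fitted as independent records, and the problem would not arise with one score per family.
- The predictors are not strictly constant within a family. Parent satisfaction is collected at 12 and 24 months, and some child characteristics change with age, so the full design effect need not apply to every predictor.

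None of this supplies the missing assumption. Clustering detail may well be left to an analysis plan, but the protocol itself states a unit, a count and a power.

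**Conclusion.** The concern holds in a conditional form. The claim of 80% power at 0.1 is not supported as stated, because it needs a low within-family correlation that the protocol neither states nor justifies. If fidelity is one score per family, the claim fails at every family count the trial could supply: about 29-35% power for one arm and 61% even for all 500 families. If sessions are nested in families, it holds only below the ICC limits shown, and any allowance for measurement error lowers them.

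The session count does not match the enrolled arm and only marginally overlaps the retained arm. No fidelity subsample of about 150 families is described.

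These conclusions assume two-sided alpha of .05, roughly equal arms and essentially family-level predictors. They concern one implementation analysis. The main effectiveness comparison and the enrolment target are unaffected.

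**What to change.** In Section 9.5:

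- State how many families, and from which arm or arms, contribute fidelity data, and recompute the session count from that number.
- Restate power in one of two ways: at family level, with a detectable coefficient of about .18-.20 for 250-200 families, or from a two-level model (sessions within families) with a stated ICC range and any allowance for measurement error.

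In Section 9.1, say whether the fidelity outcome is per session or per family. Fit the models under Moderation of Implementation Outcomes accordingly, on family-level summaries or as session-within-family models. Align the model type with Section 9.5, which names structural equation models where Section 9.1 names multivariate regression.

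Reconcile the number of sessions and the delivery period across Sections 6.1, 6.1.1, 7.1.1 and 9.5.

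The cost is some rewritten text and a less favourable stated detectable effect. No change to enrolment follows from this point.

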## Measures to Minimize Bias

### Enrollment/Randomization/Masking Procedures

***Enrollment Procedures:***

Consecutive enrollment of eligible participants, based on screening of inclusion/exclusion criteria by study staff, will take place at the SPFHC pediatric clinic. Baseline assessments, including demographic data and initial surveys/questionnaires, will be conducted at the time of enrollment, after informed consent is collected but before randomization.

***Randomization Procedures***:

Participants will be randomized into intervention (HS+PlayReadVIP) or control (standard HS) groups using a simple randomization with maximum tolderated imbalance procedure. Randomization will be conducted using a secure, centralized randomization system to ensure allocation concealment, and will be conducted by the HS+PlayReadVIP provider to ensure blinding of research staff. Randomization numbers (1 or 2) will be generated in the statistical program R using big stick design with a maximum difference between groups of 4. Numbers will be uploaded to REDCap and Research Coordinators will utilize the REDCap randomization instrument to randomly assign participants to groups based on the generated random number list.

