### Use of DataCore/Epic Information for Recruitment Purposes

This study will utilize EPIC to identify parent-child dyads for recruitment purposes.

Research Coordinators will submit weekly requests to NYULH DataCore via iLab, with up to 75 requests over the course of the study. Reports will be requested for all families with scheduled well-child visits at the NYU Langone Family Health Centers in the upcoming week at the time of request, and who meet inclusion criteria based on child current age, singleton birth, and parent primary language (PHI) and should be approached for recruitment and screening. The PI and Research Coordinators will have access to search results in order to identify potential participants. Research Coordinators will then use the following PHI identifiers to track potential participants in the clinic in order to approach them for recruitment and screening either in the clinic or by phone: name, medical record number (MRN). Data will be discarded at the end of the week for which the DataCore report was requested. All paper records will be shredded using NYULH secure shredding boxes. Electronic records, including emails, will be fully deleted from email and internal servers.

The research team will not have a treating relationship with potential participants. Once potential participants have been identified, the study team will notify the treating physician (TP) in person that they have patients eligible to participate as follow:

- Treating physician (TP) has been notified that the study team will contact potential subjects in-person in the waiting room or by phone.

Once contact is made, approved recruitment language will be used to communicate the reason they are being contacted and potential parent participants will be asked if they are interested in learning more about this specific study. Should the potential participants agree, the study team will provide the individuals with information regarding the next steps for participation.

We will discard identifying information for individuals who do not meet eligiblity criteria and for individuals who do not wish to take part in this study immediately. Deidentified information for all such individuals will be kept until study completion and reported in aggregate for CONSORT and other reporting.

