# Study Procedures and Schedule

## Study Procedures/Evaluations

**Overall Study Procedures:**

For all parent/child dyads who are enrolled in the RCT, we will administer assessments at baseline, 12 months, and 2 years to measure outcomes (e.g., parenting assets/vulnerabilities, parenting practices/parent-child relationship, child development) and covariates (e.g., socio-demographics, biological risk) for Specific Aims 1 and 2. Assessments will include a combination of parent survey, observation of parent/child, direct assessment of child, and medical record review. In addition, we will conduct two assessments with care providers within the clinic to assess intervention implementation. All assessments will be completed by highly trained research assistants blind to group/intervention status.

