### Intermediate Visits

**Visit 2 (Day 180 +/- 90)**

- Record adverse events as reported by participant or observed by investigator.
- Administer questionnaires/surveys of parent well-being, parenting, and child development, and conduct parent-child observations
- Administer questionnaires to parents and care providers regarding program acceptability, appropriateness, and reach.
- Record participant’s engagement to intervention program and program fidelity and reach.

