***Masking Procedures***:

Masking will be applied to all research staff conducting data collection assessments. Blinded research staff will not be given access to databases or materials that have the potential to reveal intervention group. Further, all databases and materials with intervention information will be clearly marked UNBLINDING, to protect against inadvertent unmasking.

Interventionists and participants cannot be masked due to the nature of the intervention.

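### The protocol names two different randomisers, one of them the role that recruits, and nothing keeps programme-experience forms away from the masked assessors

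*Protocol*

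**What the plan says.** **Who randomises.** Section 9.6.1 (Randomization Procedures) states that randomisation "will be conducted by the HS+PlayReadVIP provider to ensure blinding of research staff". The same paragraph goes on to say that "Research Coordinators will utilize the REDCap randomization instrument to randomly assign participants to groups based on the generated random number list". The list is generated by a big stick design with a maximum difference of 4 between arms. Section 5.6 gives one recruiting site and 500 dyads.

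**Who recruits.** Section 5.4.1 states that "Research Coordinators will then use the following PHI identifiers to track potential participants in the clinic in order to approach them for recruitment and screening".

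**Who is masked.** Section 7.1 states: "All assessments will be completed by highly trained research assistants blind to group/intervention status". Section 9.6.1 (Masking Procedures) states: "Masking will be applied to all research staff conducting data collection assessments", and adds: "Blinded research staff will not be given access to databases or materials that have the potential to reveal intervention group". It also says that participants and interventionists cannot be masked.

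**What happens at the outcome visits.** Section 7.1.1 (Assessment Procedures) has masked staff conduct the 12M and 24M assessments. Its questionnaire table includes the HealthySteps Parent Feedback Survey and parent satisfaction surveys at both times. The task lists for Visits 2 and 3 (Sections 7.3.3 and 7.3.4) include: "Administer questionnaires to parents and care providers regarding program acceptability, appropriateness, and reach". These stand beside the outcome surveys and the parent-child observation. Visit 3 adds qualitative interviews with parents about the programme.

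**The concern.** The two sentences on who randomises cannot both be followed. The first exists to keep research staff blind, and coordinators are research staff, so the second removes the protection that the first is meant to give. It also joins recruiting families and learning their arms in one role. Under a restricted allocation scheme, knowledge of past assignments carries information about the next one. That opens the way to selective approach or enrolment.

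The masking rule sets a low threshold: blinded staff should have no material with even the potential to reveal the arm. Parents' answers about sessions received, satisfaction and programme content have that potential, because only one arm gets video coaching. No section says who hands out these forms, how they are completed, or where they fall in the visit.

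The stake is the objective part of the evidence. Parents know their arm, and most listed outcomes are parent-reported. Videotaped observation and direct child testing are where masking protects the comparison.

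**Working it through.** **Part 1: how predictable the next arm is under the second rule**

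The protocol gives no predictability figure, so there is none to reproduce. Inputs from the protocol are two arms, a maximum imbalance of 4 (Section 9.6.1) and 500 assignments at one site (Section 5.6). Two assumptions are added: a fair coin whenever the imbalance is below 4, as the big stick design implies, and an observer who knows every earlier assignment.

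1. Let D be the running difference between arms, starting at 0. If |D| < 4, the next step is +1 or -1 with probability 1/2 each. If |D| = 4, the next assignment is forced to the lagging arm.
2. In the long run, the seven interior states (-3 to +3) each have weight 2 and the two end states each have weight 1. The total is 7 x 2 + 2 x 1 = 16, so the forced share is 2/16 = 1/8 = 12.5%.
3. Starting from balance lowers this slightly. Carrying the exact state probabilities through 500 assignments gives 61.75 expected forced assignments, and 61.75/500 = 12.35%.
4. Best-guess success is certainty on forced assignments and 1/2 on the rest: (61.75 + (500 - 61.75)/2)/500 = (61.75 + 219.125)/500 = 280.875/500 = 56.2%, against 50% by chance. The long-run value is 1/8 + (7/8)/2 = 56.25%.

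Both figures are upper bounds. An observer who sees only some of the assignments knows less.

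**Part 2: which staff meet which material**

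No arithmetic applies here; the sections are set side by side.

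| Question | What the protocol fixes | What it leaves open |
|---|---|---|
| Who does the 12M/24M assessments? | Masked research staff, for all assessments (7.1, 7.1.1) | Nothing |
| Are programme questionnaires in that battery? | Yes: HealthySteps feedback and parent satisfaction at both times (7.1.1); acceptability at Visits 2 and 3 (7.3.3, 7.3.4) | Who gives them to parents, how, and in what order |
| Are there programme interviews? | Yes, with parents, at Visit 3 (7.3.4) | Who conducts them, and whether before or after testing |
| Are provider surveys separate? | Yes, completed online (Care Provider Study Procedures) | Nothing relevant here |
| Are fidelity and engagement collected by masked staff? | Not stated; fidelity is monitored through sessions (6.1.2), and both are tracked from the medical record (9.4.2) | Who records them at the visits |
| Are the video coders masked? | Observations are videotaped and globally coded (7.1.1) | Whether coders are separate and masked |

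Read literally, masked staff run a visit containing forms that could reveal the arm, and the masking section bars them from such material. Nothing else in the protocol resolves this.

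**The case against.** **On allocation.** The list sits in a centralised REDCap system, enrolment is consecutive, and consent and baseline assessment precede randomisation. Coordinators are referred to in the plural, so one person may not see every assignment. A guess rate of 56% is about six points above chance. All of this stands and limits the harm, which is why the figures are given as upper bounds. It does not reconcile the two sentences, and a concealed future list does not hide what past assignments imply.

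**On the forms.** Both arms receive HealthySteps, and Section 9.1 compares acceptability between arms, so receiving such a form does not identify the arm. Item content is not shown, and parents may complete the forms themselves. This also stands, and is why the second part is only a risk. Self-completion is not stated, however, and Sections 2.3.1 and 5.3.1 train examiners to help parents who cannot read the questionnaires.

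**On the path to bias.** Parent-child interaction is coded from video, so the rater need not have been at the visit. That is a fair limit. The exposure lies mainly in direct child testing, where the picture vocabulary tests come only at 2 years, and in other live assessment.

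**Stronger readings that a reader might infer.**
- That masked assessors have to handle fidelity records. The visit lists name no one, and Sections 6.1.2 and 9.4.2 point to session monitoring and the medical record.
- That coordinators are unmasked outcome assessors. No section gives them that task. Their knowing the arm conflicts with the stated blinding of research staff but does not by itself unmask an assessor.
- That the bias can be expressed in standard deviations. The documents offer no basis for such a figure.

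**Conclusion.** The point holds in two parts of unequal strength.

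1. The contradiction over who randomises is plain on the page. If the coordinator sentence is followed, the recruiting role learns assignments, and at most about 62 of 500 (12.4%) are predictable with certainty, with overall guess success of about 56%. This rests on one person seeing all earlier assignments and knowing the limit of 4.
2. The missing separation between masked assessors and programme-experience material conflicts with the protocol's own masking rule. It is a risk, mainly for direct child testing and live assessment. The documents do not show that unmasking would occur, and its effect on the estimates cannot be sized from them.

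The baseline assessment is unaffected, since it precedes randomisation. The first part should be settled before assignments are made, because concealment once lost cannot be restored.

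**What to change.** **Randomisation.** Keep one sentence in Section 9.6.1. It should name a single existing unmasked role that triggers REDCap randomisation and has no recruitment, eligibility or outcome-assessment duty. Deleting the coordinator sentence may not be enough. Section 6.1.1 has HealthySteps Specialists deliver the combined model, and the Protocol Summary has the HealthySteps Specialist identify Tier 3 families, which is an entry criterion. A provider in that position would also influence entry and see assignments. The protocol does not identify a role that clearly qualifies, so the sponsor must designate one. Set REDCap rights so that recruiters and assessors cannot view assignments or arm totals.

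**Visits 2 and 3.** State that observation, direct testing and effectiveness questionnaires are completed first. Programme satisfaction, feedback and acceptability forms then follow by self-completion or through unmasked staff, who also help any parent needing reading support. Hold the qualitative interviews separately. State that video coders are masked.

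**Cost.** Protocol wording, REDCap user rights and slightly more visit coordination. Sample size, measures and analyses do not change.
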